### Objectives

The main purpose of the ongoing trial is to determine the efficacy of the manualized STPP regarding remission of depression in breast cancer patients. Secondary outcomes refer to changes of quality of life and to the effect of subtype of depression on treatment outcome.

Based on non-responder analyses we intend to answer the question, which patients do not accept psychotherapeutic treatment for what reason and which characteristics (e.g. age, marital, social status, illness variables, type of depression) have an impact on treatment outcome?

### Hypotheses

Primary outcome:

1) Higher rate of remission in STPP vs. ‘treatment as usual’ (TAU) at treatment termination.

Secondary outcomes:

2) Six months after the end of treatment lower rate of depression and a higher quality of life among the STPP group compared to TAU.

3) Better outcome in dependent/anaclitic vs. self-critical/ perfectionistic depression (DEQ).

### Study design

In the multicenter randomized prospective trial breast cancer patients with comorbid depression who fulfill inclusion criteria either get STPP or TAU. Figure
1 gives an overview of the study design, time-points of assessments measures used and projected numbers.

**Figure 1 F1:**
[figure not shown]
**Study design and patient recruitment (N = projected numbers).** Notes: a) Questionnaires filled out by the patients; b) Structured Clinical Interview for DSM-IV applied by trained interviewers; c) HADS score for depression ≥ 8 & SCID-I diagnosis estimated in 20% of the cases (N = 240 eligible patients) of whom 75% are expected to be consent with randomization; d) Expected completer 80%, e) Expected completer 70%.

We plan to recruit N = 90 participants per group. To ensure adequate randomization stratified for the center, the random assignment to STPP or TAU was performed separately by research staff from the responsible center (not engaged in the project) using a computer-generated
[25] number series of random length (contained within closed, opaque envelopes.).

STPP entails five pre-treatment and up to 20 therapeutic sessions over a period of six months. In each center a close collaboration was established with about 10 psychodynamic psychotherapists in private practice who were trained according to the manual and supervised on a regular basis. Intensive training (at least 2 x 2 hours) is performed in a group format by the respective local study center prior to entering the first patient. Supervision is performed on a monthly basis (3 hours) in the group. In order to assure adherence to the manual, it is recommended that therapists present patients in supervision three times (initial formulation of CCRT based on relationship episode interview, middle and termination phase of treatment).

Patients randomized to the TAU condition are not offered STPP, but obtain written information on local cancer counseling centers and get written information on psychodiagnostic findings to their general practitioner who may then initiate antidepressant treatment (‘as usual’). Utilization of medical, psychotherapeutic and psychopharmacological treatment is documented throughout the study.

### Outcome

Remission of depression is defined by reduction of the HADS depression-score (at least by 2 points) and remission of depression (SCID-I-diagnosis) at treatment termination.

### Sample size calculation

While planning this study no meaningful published data on remission rates for STPP vs. TAU for the treatment of depression in breast cancer were available. For STPP of depression remission rates between 45% and 70% at post-therapy assessment were published
[26], while remission rates in primary-care settings (comparable to TAU) ranged between 20% and about 50% (6 months)
[27-29]. For patients with complex medical illness like cancer and co-morbid depressive disorders we expect lower remission rates for TAU and also for STPP. For this highly burdened population we pragmatically expected a spontaneous remission rate of 25% for TAU and 50% for STPP in our sample size calculation.

In order to identify group differences of 25% (25% remission in TAU vs. 50% in STPP) as based on χ2-Test (two-tailed) and a power of 0.80 a total sample of N = 156 is required, taking into account a slightly higher dropout rate of 30% in the TAU group vs. a 20% in STPP.

### Statistical analyses

The primary endpoint remission after the treatment phase will be analyzed by a logistic regression with fixed effects for treatment and center and the baseline HADS value as covariate. The primary population for analysis will be the population intended to treat (ITT) consisting of all randomized patients. Dropouts will be regarded as non-remitters. For sensitivity the analysis will be repeated for the completers of treatment population. Additionally, the single components (HADS improvement of ≥2 points, remission according to SCID) will be analyzed separately by the same analysis model as the combined endpoint.

Secondary analyses include the remissions at the end of the follow-up. Remissions at the end of the follow-up will be evaluated accordingly. The quality of life (QoL) questionnaires will be analyzed by an analysis of covariance (ANCOVA) model with fixed effects for treatment and center and the baseline values (HADS depression score & Qol) as covariates. It is expected that the QoL questionnaires will not be linear across the study. Therefore QoL questionnaires after the follow-up will be evaluated by a linear model with fixed effects for treatment, center and time. There will be an indicator variable for the post treatment visit. The HADS value at baseline will serve as a covariate. For QoL data the observed values will be analyzed. However, if the number of missing data is more than 10%, the data will be evaluated after multiple imputation of the data by a Markov chain Monte Carlo (MCMC) method. The impact of moderator variables (age, marital, social status, illness variables, type of depression) is tested in regression analyses.

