**Methods/design:**

Eligible breast cancer patients with comorbid depression are assigned to short-term psychodynamic psychotherapy (up to 20 + 5 sessions) or to treatment as usual (augmented by recommendation for counseling center and physician information). We plan to recruit a total of 180 patients (90 per arm) in two centers. Assessments are conducted pretreatment, after 6 (treatment termination) and 12 months (follow-up). The primary outcome measures are reduction of the depression score in the Hospital Anxiety and Depression Scale and remission of depression as assessed by means of the Structured Clinical Interview for DSM IV Disorders by independent, blinded assessors at treatment termination. Secondary outcomes refer to quality of life.

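### Therapist clustering in the STPP arm is absent from the stated models, so the treatment standard error is too small if outcomes differ between therapists

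*Protocol article*

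**What the plan says.** Under Statistical analyses, the primary endpoint (remission after treatment) is to be analyzed by "logistic regression with fixed effects for treatment and center and the baseline HADS value as covariate". The two single components and remission at the end of follow-up take the same model. Quality of life is to be analyzed by an ANCOVA "model with fixed effects for treatment and center and the baseline values (HADS depression score & Qol) as covariates". The follow-up quality-of-life data "will be evaluated by a linear model with fixed effects for treatment, center and time", with baseline HADS as covariate. None of these models has a therapist effect or a variance that allows for clustering.

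On delivery of treatment, Study design states: "In each center a close collaboration was established with about 10 psychodynamic psychotherapists in private practice". The abstract gives the size: "We plan to recruit a total of 180 patients (90 per arm) in two centers". For the control arm, Study design states: "Patients randomized to the TAU condition are not offered STPP".

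**The concern.** STPP is individual therapy, and each therapist treats several trial patients. Patients of the same therapist may have outcomes more alike than patients of different therapists. TAU patients are not grouped by study therapist, so the design is partially nested: clustered in one arm, independent in the other.

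The stated models treat all STPP patients as independent. The fixed center effect takes out the average difference between the two centers and leaves the variation among the roughly 10 therapists within each. If that variation is not zero, the STPP arm holds less information than the model assumes. The confidence interval is then too narrow and the primary test rejects a true null too often, in either direction, so a false claim of benefit becomes more likely. The article itself treats the quality of the therapeutic relationship as a driver of outcome (Background) and has therapist adherence and competence rated (Assessments), so therapist variation is not far-fetched here.

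**Working it through.** **Does the plan's own figure allow for clustering?** Inputs from Sample size calculation: 25% vs 50% remission, two-tailed χ² test, power 0.80, dropout 30% (TAU) and 20% (STPP). Alpha is not stated; 0.05 is assumed.

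- n per arm = [1.96·√(2·0.375·0.625) + 0.8416·√(0.25·0.75 + 0.50·0.50)]² / 0.25² = (1.342 + 0.557)² / 0.0625 = 57.7, rounded up to 58.
- TAU: 58/0.70 = 83. STPP: 58/0.80 = 73. Total 156, exactly as stated.

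The figure is reproduced under full independence, so it contains no design effect.

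**Size of the effect.** Inputs: 2 × 10 = 20 therapists; 90 per arm; m = 90/20 = 4.5 patients per therapist. The ICC is an assumption, 0.01 to 0.20.

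- Design effect in the STPP arm: D = 1 + (m − 1)·ICC = 1 + 3.5·ICC.
- With equal arms, true SE / model SE = R = √[(1 + D)/2].
- Type I error of the unadjusted test = 2·[1 − Φ(1.96/R)].

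| ICC | D | R | Type I error, formula | Type I error, rounded with simulation |
|---|---|---|---|---|
| 0.01 | 1.035 | 1.009 | 5.2% | 5.2% |
| 0.02 | 1.070 | 1.017 | 5.4% | 5.4–5.6% |
| 0.05 | 1.175 | 1.043 | 6.0% | 6.1% |
| 0.10 | 1.350 | 1.084 | 7.1% | 7.2% |
| 0.15 | 1.525 | 1.124 | 8.1% | 8.2% |
| 0.20 | 1.700 | 1.162 | 9.2% | 9.3% |

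The simulation draws therapist-level remission rates from a beta distribution and applies an unadjusted two-proportion test. It stands in for the planned logistic model.

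**Uneven caseloads.** With an assumed coefficient of variation of 0.6, D = 1 + [(1 + 0.36)·4.5 − 1]·ICC = 1 + 5.12·ICC. At ICC 0.05/0.10/0.15/0.20, D = 1.256/1.512/1.768/2.024 and the type I error is about 6.5/8.0/9.6/11.1%.

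**Dropouts counted as non-remitters.** If 20% drop out for reasons unrelated to therapist, and remission is otherwise 35% in both arms (assumed), the ICC of the analyzed outcome shrinks by the factor 0.8·(1 − 0.35)/(1 − 0.8·0.35) = 0.52/0.72 = 0.72. The type I error with equal caseloads is then about 5.6/6.3/7.2/8.1% at the same four ICC values by simulation; the formula agrees within 0.2 points.

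**Power.** Replacing 90 STPP patients by 90/D, power for 25% vs 50% falls from 0.940 to 0.921 at ICC 0.05 and 0.880 at 0.15. With remission diluted by the expected dropout (25%·0.70 = 17.5% vs 50%·0.80 = 40%), it falls from 0.922 to 0.901 and 0.857.

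**The case against.** The strongest objection is that the harm is conditional. The document gives no ICC, and it describes a manual, training before the first patient, monthly group supervision and adherence ratings from videotapes, all of which aim to make therapists alike. At an ICC of 0.01 or 0.02 the distortion is trivial. This stands: a reader might infer that the primary test certainly exceeds its 5% level, and the document does not support that. These measures may shrink therapist variance, but they do not show that it is zero, and the analysis makes no provision for what remains.

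Second, the planned analysis is milder than a simple calculation suggests. Counting dropouts as non-remitters dilutes the clustering, and the center effect removes any between-center part. Both points stand and lower the figures somewhat. Dropout that depends on the therapist would undo some of the dilution, and uneven caseloads work the other way.

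Third, such detail might be left to a statistical analysis plan. That does not hold here, because the article lists the terms of each model and a faithful analysis plan would carry them over.

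A reader might also infer that the trial is underpowered. At the planned 90 per arm with equal caseloads, power stays at about 0.86 or more up to an ICC of 0.15 in the intention-to-treat setting. Analyzing only the expected completers (63 and 72) gives 0.849 to 0.797 at ICC 0.02 to 0.15. Power is not the main issue.

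**Conclusion.** The point holds in conditional form. The stated primary and quality-of-life models ignore a known one-arm clustering, and their treatment standard error is too small whenever the therapist ICC is above zero. For an assumed ICC of 0.01 to 0.20, 20 therapists and equal caseloads, the standard error is too small by a factor of 1.01 to 1.16 and the type I error is about 5.2% to 9.3%. It is higher with uneven caseloads and lower with therapist-independent dropout. The missing allowance is certain; the size of its effect is not, since it rests on ICC and caseload assumptions that the document does not supply.

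A reader might go on to infer that the result could not be generalized beyond the recruited therapists. That is too absolute. What follows is narrower: formal statistical inference to other therapists requires therapist variance in the error term. This is relevant because the Discussion anticipates transferring the manual to other cancers. The change is worth making, but the flaw does not undermine the trial.

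**What to change.** In Statistical analyses, keep the stated fixed effects and covariates and add that standard errors for remission (combined endpoint, components and follow-up) and for quality of life are clustered by therapist. Name one small-sample correction, for example a bias-reduced cluster-robust variance with t-based degrees of freedom. Define the clusters: STPP patients belong to their therapist, including those who drop out after starting; each TAU patient, and each STPP patient who never started with a therapist, is a cluster of one patient. This keeps the planned odds ratio as the estimand.

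Report the therapist ICC. Add a partially nested model, with a therapist random effect in the STPP arm only, as a sensitivity analysis. It should not replace the main model: its odds ratio is conditional on therapist, and with 4 to 5 patients each the therapist variance may be estimated at zero.

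The cost is slightly wider intervals, a small loss of power and some added analysis work. No new data collection should be needed, since STPP patients are presented in supervision and every session is videotaped, so the treating therapist is known.

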
### Assessments

At baseline, patients fill out the HADS
[15] in the German version (HADS-D)
[16], a standardized questionnaire devised for the assessment of depression and anxiety in somatic illness with 14 items. Quality of life is assessed by the generic 30-item questionnaire of the European Organization for Research and Treatment of Cancer Quality of Life Questionnaire - Core 30 (EORTC QLQ-C30)
[17] differentiating a global health status, functioning (physical, role, emotional, cognitive, social) and symptoms (e.g. fatigue, nausea and vomiting, pain etc.). Furthermore, the breast cancer specific quality of life module (EORTC QLQ-BR23)
[18] which consists of functional scales (body image, sexual functioning, sexual enjoyment, future perspective) and symptom scales (system therapy side effects, breast symptoms, arm symptoms and upset by hair loss) is used. The validated German version of the Depressive Experience Questionnaire (DEQ)
[19] is used to identify prognostically relevant personality dimensions of dependency (loneliness, helplessness, fear of rejection), perfectionism or self-criticism (worthlessness, failure, guilt, critical self-monitoring) and self-efficacy (ambitious, competitive and self-reliant stance). The Multidimensional Fatigue Inventory (MFI)
[20] is a 20 item self-report instrument covering the dimensions general fatigue, physical fatigue, reduced activity, reduced motivation and mental fatigue. The German version
[21] of the Helping Alliance Questionnaire (HAQ)
[14] an 11-item rating scale for assessing perceptions of the therapeutic relationship and process is filled out by the patient and therapist at the end of psychotherapy. The Structured Clinical Interview for DSM-IV
[22] is used for standardized (‘gold standard’) assessment of axis I diagnoses. The PACS-SE (Penn Adherence/Competence Scale) with 45 Items
[23] is used in the German version
[24] for independent assessment of therapist adherence and competence based on randomly selected videotaped therapy sessions.

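### The follow-up quality-of-life model names only baseline HADS as covariate, although the ANCOVA also uses baseline QoL; the 12-month comparison loses precision, by an amount the document cannot fix

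*Protocol article*

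**What the plan says.** The protocol article, under Statistical analyses, describes two models for the same QoL questionnaires.

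- **ANCOVA.** It has "fixed effects for treatment and center and the baseline values (HADS depression score & Qol) as covariates". No visit is named. The contrast with the next model suggests treatment termination (month 6), but that is an inference.
- **Follow-up model.** "QoL questionnaires after the follow-up will be evaluated by a linear model with fixed effects for treatment, center and time". Then: "There will be an indicator variable for the post treatment visit". The covariate sentence is "The HADS value at baseline will serve as a covariate". Baseline QoL is not named, and neither is a treatment-by-time term.

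The change of model is explained by an expected non-linear course of QoL over the study. That explains the coding of time; it says nothing about the covariates.

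Hypothesis 2 places the QoL claim at the later time point: "Six months after the end of treatment lower rate of depression and a higher quality of life among the STPP group compared to TAU". The follow-up model is the one that reaches it. Under Assessments, the QLQ-C30 and the breast cancer module are among the baseline instruments.

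**The concern.** The baseline value of a scale is usually a strong predictor of its later value. The plan uses it in one QoL model and does not name it in the other, and the other is the model that covers the time point of hypothesis 2. If the follow-up model is fitted to post-baseline visits as written, its residual variance is larger than it need be. Seen conditionally on the sample drawn, a chance difference in baseline QoL between the arms, so far as HADS does not explain it, stays partly in the treatment estimate.

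This is not a detail left to a later document: the article fixes a covariate list for each model, and the lists differ. At stake is the precision of a secondary comparison. The primary remission analysis is not affected.

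**Working it through.** **The plan's own figure.** There is none for QoL: no SD, effect size, correlation or power. The only sample size concerns remission, and it reproduces. For 25% against 50%, power 0.80 and two-sided alpha 0.05 (alpha assumed), the chi-square formula gives 58 per arm; 58/0.70 = 83 and 58/0.80 = 73, total 156. It does not bear on QoL.

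**Inputs**
- From the document: "We plan to recruit N = 90 participants per group"; dropout 20% (STPP) and 30% (TAU). This leaves 90 × 0.80 = 72 and 90 × 0.70 = 63 patients.
- Assumed: true 12-month difference 0.4 SD; two-sided alpha 0.05; correlation r of baseline with 12-month QoL of 0.3, 0.5 or 0.7. For baseline HADS, two cases: (a) -0.5 with baseline QoL and -0.3 with 12-month QoL; (b) -0.2 and -0.15.

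**Reading 1: post-baseline outcomes, taken as a 12-month comparison**

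Write h for the correlation of HADS with 12-month QoL and g for that of HADS with baseline QoL.
- Residual variance with HADS only: 1 - h². Case (a): 0.910. Case (b): 0.9775.
- Residual variance with both: 1 - (r² + h² - 2rhg)/(1 - g²).
- Example, r = 0.5, case (a): 1 - (0.25 + 0.09 - 0.15)/0.75 = 0.747. Ratio 0.747/0.910 = 0.82.
- Power: Φ(0.4/√(v(1/72 + 1/63)) - 1.96), with v the residual variance.

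| r | Variance ratio (a), (b) | Cut | Power, HADS only | Power, both |
|---|---|---|---|---|
| 0.3 | 0.97, 0.92 | 3-8% | 0.65-0.68 | 0.69-0.70 |
| 0.5 | 0.82, 0.76 | 18-24% | 0.65-0.68 | 0.77 |
| 0.7 | 0.56, 0.52 | 44-48% | 0.65-0.68 | 0.90 |

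At r = 0.5 the cut equals 22-31% more patients (1/0.82 and 1/0.765).

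Other assumptions give the same direction. With 0.5 SD, 63 per arm, r = 0.5 and case (a), power goes from 83.7% to 90.1%. Across r from 0.3 to 0.7 and HADS correlations from zero to -0.4 with 12-month QoL (-0.6 with baseline QoL), the gain runs from 0.2 to 17.4 points.

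*Chance imbalance.* The SD of the baseline difference between arms is √(1/72 + 1/63) = 0.17 SD. At r = 0.5, case (a), the coefficient of baseline QoL given HADS is (0.5 - 0.15)/0.75 = 0.47. A difference of 0.2 SD that HADS does not explain would thus leave about 0.09 SD in the HADS-only estimate.

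**Reading 2: baseline QoL as a response**

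Intercept, time and the post-treatment indicator make three columns. With visits at 6 and 12 months their rank is 2, so one term is redundant. With 0, 6 and 12 months the rank is 3. The stated coding therefore fits a three-visit model better.

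In that model, with one treatment effect common to all visits and equal weights:
- A true effect of 0, 0.5 and 0.5 SD at the three visits is estimated as (0 + 0.5 + 0.5)/3 = 0.33 SD.
- With 63 per arm and correlation 0.5 between all visits, the variance of a patient's mean is (1 + 2 × 0.5)/3 = 0.667. The standard error is √(0.667 × 2/63) = 0.145, and power is Φ(0.333/0.145 - 1.96), about 63%. A 12-month ANCOVA with baseline QoL would have about 90%.
- A baseline imbalance of 0.2 SD enters as 0.2 × (1 + 0.5 + 0.5)/3 = 0.13 SD.

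**The case against.** The strongest reply is that baseline QoL was left out on purpose. Time plus a post-treatment indicator makes sense only with three visits, so baseline QoL is probably a response, and a response is not normally its own covariate. This is plausible, and it defeats the inference that the omission must be a slip without reason. It does not rescue the text: the model states neither a treatment-by-visit term nor equal baseline means, and without them Reading 2 dilutes the effect. If both were stated, most of the loss would disappear.

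Three stronger readings may tempt a reader, and the document supports none of them.
- *The 12-month result would be biased, or its test invalid.* Under Reading 1, randomization keeps the estimate unbiased on average and type I error intact.
- *The 6- and 12-month effects would not be comparable.* In linear models under randomization, both adjustments target the same mean difference; precision differs.
- *Lost power and retained imbalance are two separate harms.* They are largely one: random imbalance is already in the HADS-only standard error.

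It is also right that the figures rest wholly on assumed correlations, and that adding one covariate would not by itself give hypothesis 2 a 12-month test. The fix has to go further than that.

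**Conclusion.** The point holds as one of precision and clarity on a secondary endpoint. The two QoL models name different baseline covariates, and the weaker set belongs to the model that reaches the time point of hypothesis 2.

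Under Reading 1 the avoidable loss is anything from negligible (3% of residual variance) to substantial (48%), depending on a correlation that the document does not give. The figures treat month 12 as a single-visit comparison. Under Reading 2 the loss comes from averaging the treatment effect over a visit before treatment, and baseline imbalance enters the estimate directly. The wording does not settle which model is meant, and neither reading gives a contrast specific to month 12. The change is worth making, but the conclusion on remission does not depend on it.

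**What to change.** In the QoL paragraph of Statistical analyses, replace the description of the follow-up model along these lines: *The 6- and 12-month values of each QoL scale are the outcomes of a linear model with treatment, center, visit and treatment-by-visit. The baseline HADS depression score and the baseline value of the respective QoL scale are covariates. The treatment contrast at 12 months tests hypothesis 2.*

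This makes four changes: baseline QoL becomes a covariate, as in the ANCOVA; baseline is removed as a possible response; time and the post-treatment indicator become one visit term; and hypothesis 2 gets its own contrast. It would also help to name the visit to which the ANCOVA applies.

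The cost is a few degrees of freedom per model and no new data.
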